#### 6.3.3. Secondary Endpoints

A secondary endpoint is the construction of mathematical models for the correlation of proteomic, metabolomic, and lipidomic data with clinical data of the three patient populations (non-metastatic PCa, BPH, and mHSPCa).

### 6.4. Population and Eligibility Criteria

Three different populations will be considered and compared.
-Subgroup 1: Patients with initial histological diagnosis from prostate biopsy of PCa considered for radical prostatectomy as primary therapy, as a therapeutic choice shared with the doctor and in accordance with international guidelines. This treatment will follow normal clinical practice for this pathology and regular clinical and therapeutic procedure. Staging of these patients will be non-metastatic PCa at imaging (multiparametric magnetic resonance of the prostate).-Subgroup 2: Patients with initial histological diagnosis from prostate biopsy of advanced metastatic PCA (mHSPC) to be subjected to standard pharmacological treatments with androgen deprivation (ADT) and new androgen-targeted treatments (ARPI) or chemotherapy with taxanes, as a therapeutic choice shared with the doctor and in accordance with international guidelines. This treatment will follow normal clinical practice for this pathology and regular clinical and therapeutic procedure. Staging of these patients will be metastatic at imaging (PET CT scan or bone scan and CT scan).-Subgroup 3: Patients with initial diagnosis of BPH who have not undergone treatments. A healthy control population is not included but the BPH population will be used as a control. The clinical comparison will use male subjects of the same age (40–75 years) to determine the expression of a potential marker for prostatic neoplasia, involving the evaluation of differences within a population with benign prostatic pathology such as BPH and not healthy subjects (those without BPH) of mismatched age.

#### 6.4.1. Subgroup 1 and 2

Inclusion criteria: Male patients aged between 40 and 75 years, of any ethnicity, with an initial histological diagnosis of PCa from prostate biopsy. Non-metastatic versus metastatic clinical stage, intermediate or high-risk class according to d’Amico, indication as primary treatment for radical prostatectomy (Subgroup 1) or systemic therapy with androgen deprivation and ARPI or taxanes (Subgroup 2).

Exclusion criteria: Local or systemic therapies for PCa, other neoplasms in the active phase or undergoing treatment, ongoing oncological therapies (chemotherapies, target therapies, radiotherapies), hormonal or steroid therapies in progress or with drugs known to interfere with the evaluation foreseen in the study.

#### 6.4.2. Subgroup 3

Inclusion criteria: male patients aged between 40 and 75 years, of any ethnicity, with an initial diagnosis of BPH.

Exclusion criteria: local or systemic therapies for BPH, suspicion or diagnosis of prostatic neoplasia, other neoplasms in the active phase or undergoing treatment, ongoing oncological therapies (chemotherapies, target therapies), hormonal or steroid therapies in progress or with drugs known to interfere with the assessment intended for the study.

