PEGylated polystyrene nanoparticles (PEG-PNs) are widely used to evaluate the influence of protein corona composition in patients with non-small cell lung cancer (NSCLC) [12]. In 2022, Xu W et al. used PEG-PNs to evaluate the influence of protein corona composition in patients with NSCLC and type 2 diabetes mellitus (T2DM) compared with that of patients with NSCLC alone [12]. They collected human plasma samples which were isolated by centrifugation from heparinized venous blood, obtained from the two groups of patients. Then, fluorescent labeled polystyrene NPs were synthesized by microemulsion polymerization and subsequently modified with PEG and transferrin (Tf) to create PEG-NPs and Tf-NPs. These PEG-NPs and Tf-NPs were cultured with plasma from patients in the NSCLC with comorbidity group to obtain derived protein coronas–NPs. Thus, different NPs’ coronas were characterized using nano-liquid chromatography–tandem mass spectrometry. PEG-NPs and Tf-NPs were intravenously injected into mice with NSCLC and mice with NSCLC comorbid with T2DM to study NPs’ behavior in vivo using fluorescence imaging. The way the state of the disease affected NPs’ distribution was then evaluated: NPs accumulated in the tumor tissue at 1 h post-injection and remained in the tumor area for 24 h. In particular, Tf-NPs exhibited higher accumulation in tumor tissue than PEG-NPs and higher accumulation in the NSCLC comorbid with T2DM group than in the NSCLC group. Furthermore, researchers investigated the cellular uptake of various types of protein-coated NPs in A549 cells (a model for NSCLC), including bare NPs (PEG- and Tf-NPs), those coated with human plasma-derived proteins from NSCLC patients, and those from NSCLC patients with T2DM. A549 cells showed a time-dependent increase in NP uptake: Tf-NPs had higher uptake than PEG-NPs at 1 h and 2 h (*p* < 0.01). Pre-treatment with free Tf reduced Tf-NP uptake, suggesting that Tf-receptor-mediated endocytosis is the likely pathway for uptake. Tf-NP-coated coronas from individuals with NSCLC comorbid with T2DM showed greater accumulation in A549 cells. This study highlights how the comorbidity clinical status of patients influenced the protein corona composition, thereby affecting the bio-behavior of NPs [12]. Notably, Tf-NPs demonstrated greater accumulation in NSCLC groups comorbid with T2DM, providing insight into how the disease state plays a pivotal role in determining the distribution of nanoparticles. Furthermore, the interaction between cellular receptors and nanoparticle surface ligands is crucial in shaping the biological fate of nanoparticles. NSCLC comorbid with T2DM-derived protein coronas contain more fibrin and polyproteins, which may help nanoparticles evade non-characteristic intake [12].

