
### 6.2. Study Design

We developed the design of an experimental prospective single-center study with patients allocated in a 1:1:1 ratio of one of the three arms. A longitudinal analysis will also be applied to a 12-month interval observation. The protocol has been approved by our Ethic Committee Sapienza Policlinico Umberto I, Prot 0919/2021. The protocol will start on January 2025.

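### A shared 40–75 year entry range is treated as equal age, so part of any PCa-versus-BPH separation could be age rather than cancer

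*Protocol article*

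**What the plan says.** Section 6.4 justifies BPH patients as the control group. It says "The clinical comparison will use male subjects of the same age (40–75 years" and sets this against using "not healthy subjects (those without BPH) of mismatched age". The article therefore treats a difference in age as something the control group should avoid.

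The criteria behind that statement are the same entry range in every group:
- Subgroups 1 and 2 (section 6.4.1): "Male patients aged between 40 and 75 years, of any ethnicity, with an initial histological diagnosis of PCa from prostate biopsy".
- Subgroup 3 (section 6.4.2): "male patients aged between 40 and 75 years, of any ethnicity, with an initial diagnosis of BPH".

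The article describes no age bands, matching or strata. Section 6.2 describes a design "with patients allocated in a 1:1:1 ratio of one of the three arms", but the arms are diagnoses.

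On comorbidity, section 3 summarises a lung cancer study and concludes: "This study highlights how the comorbidity clinical status of patients influenced the protein corona composition". More specifically, "NSCLC comorbid with T2DM-derived protein coronas contain more fibrin and polyproteins". The nearest eligibility rule is about drugs. Section 6.4.2 excludes "hormonal or steroid therapies in progress or with drugs known to interfere with the assessment intended for the study", with a near-identical rule for the cancer groups. No drug is named, and diabetes is not mentioned.

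**The concern.** A common range fixes the youngest and oldest permitted age and nothing between. Men with newly diagnosed untreated BPH, men chosen for prostatectomy and men presenting with metastatic disease reach the clinic by different routes, so their ages may differ within 40–75. The 1:1:1 ratio cannot correct this. It equalises group sizes, while diagnosis decides who belongs to which group.

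The first primary endpoint (section 6.3.2) is a diagnostic model for PCa versus BPH. Section 6.6 expects patterns specific to the pathological condition and plans PCA, OPLS-DA and PLS-DA to find them. A supervised classifier uses whatever separates the labels. If the groups differ in age and some corona features follow age, those features can be selected and reported as cancer markers. Cross-validation would not reveal this, because every fold carries the same age imbalance.

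**Working it through.** **No figure to reproduce.** The article gives no sample size, effect size or age distribution. The text was checked by reading it. The possible size below is an illustration on assumed inputs.

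**Step 1: what the range fixes.** The window is 75 − 40 = 35 years wide. Two groups can both lie wholly inside it and still have different mean ages.

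**Step 2: age alone.** Assume normal ages with equal SD in both groups. Then AUC = Φ(gap / (SD × √2)).

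| Mean gap (years) | SD 8 | SD 7 |
|---|---|---|
| 3 | Φ(3/11.31) = 0.605 | Φ(3/9.90) = 0.619 |
| 5 | Φ(5/11.31) = 0.671 | Φ(5/9.90) = 0.693 |
| 8 | Φ(8/11.31) = 0.760 | Φ(8/9.90) = 0.790 |

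Rounded, these are about 0.61, 0.68 and 0.78. If age is the only difference between the groups, no panel that merely reflects age can exceed them.

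**Step 3: respecting the entry limits, and one imperfect marker.** Ages were simulated as normal with SD 7, truncated to 40–75. The marker has correlation 0.5 with age and no cancer effect. Its standardised group difference d gives AUC = Φ(d/√2). The last column is the chance of a nominal finding in the direction of the age effect (two-sided 5% test, no multiplicity correction) with an assumed 100 men per group.

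| Realised mean gap (years) | AUC, age alone | d, marker | AUC, marker | Chance of nominal significance |
|---|---|---|---|---|
| 0 | 0.50 | 0.00 | 0.50 | 0.03 |
| 2.6 | 0.61 | 0.199 | 0.56 | 0.29 |
| 4.2 | 0.68 | 0.315 | 0.59 | 0.61 |
| 6.7 | 0.77 | 0.482 | 0.63 | 0.93 |

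With 50 men per group, the last column for the three non-zero gaps is 0.17, 0.35 and 0.67. The zero-gap row shows what matching would achieve.

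**Step 4: diabetes.** Assume a marker that shifts by 1 SD in diabetic men and has no cancer effect. The group shift is (p₁ − p₀) × 1 SD.
- Prevalence 10% versus 20%: shift 0.10, AUC 0.53.
- Prevalence 10% versus 30%: shift 0.20, AUC 0.55.
- Equal prevalence: AUC 0.50.

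Per feature, and on these assumptions, this is smaller than the larger age effects.

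**The case against.** The strongest reply has five parts.

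1. **Adjustment may be planned elsewhere.** A journal article condenses the protocol, and covariates normally sit in the analysis plan, which is not shown. This stands. A reader might infer from section 6.6 that the analysis will be unadjusted, but the document cannot show that. The point therefore rests on what section 6.4 asserts about age, not on missing covariates.

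2. **The diabetes evidence is indirect.** A reader might infer that the article shows diabetes on its own to change the corona and that the trial disregards it. Neither holds. The cited study compared lung cancer plus type 2 diabetes with lung cancer alone, on modified polystyrene particles; this trial uses three liposomes. Diabetes would also need to differ in prevalence between PCa and BPH, and nothing in the document says it does. The interfering-drug exclusion, the fasting morning sample (section 6.5) and the secondary endpoint relating omics to clinical data (section 6.3.3) show some attention to such variation. None of them balances diabetes.

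3. **The document never says that age alters the corona.** Correct. It only treats mismatched age as undesirable.

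4. **Age is not the only reason for BPH controls.** Also correct. Sections 6.3.1 and 6.4 make PCa versus benign disease the clinical question, and the choice of BPH controls is not criticised here.

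5. **Every numerical input is assumed.** True. The AUCs in step 2 belong to age itself, and a corona panel reaches them only if it encodes age almost perfectly.

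None of this rescues the assertion that a common 35-year range makes the men the same age.

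**Conclusion.** The point holds in limited form. Section 6.4 claims age comparability, and recruiting as it describes does not deliver it. Part of an observed PCa-versus-BPH separation could therefore be due to age.

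This is a risk, not a demonstrated bias. It depends on a real age gap between the groups and on corona features that follow age, and the document quantifies neither. With SD 7–8 years and gaps of 3 to 8 years, the ceiling from age alone is an AUC of about 0.61 to 0.78. A single marker correlated 0.5 with age reaches about 0.56 to 0.63 over simulated gaps of 2.6 to 6.7 years. These figures should not be read as the expected performance of a corona panel without cancer information.

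Diabetes is secondary. The article reports that it altered the corona in another cancer and on other particles, and the eligibility criteria neither restrict nor balance it. Its size and direction in this trial are unknown. The age issue affects the first primary endpoint and is cheap to correct, so it should be corrected.

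**What to change.** - **Section 6.4:** replace the statement about equal age with frequency matching of Subgroup 3 to Subgroup 1 in 5-year age bands. If Subgroup 2 is also compared with BPH, apply the same bands to it or adjust that comparison for age.
- **Data collection:** record diabetes status from the chart. Age is already needed for eligibility.
- **Section 6.6 or the analysis plan:** fit a model with age and diabetes alone, add the corona features in the same cross-validation folds, and report the gain in cross-validated AUC.

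The cost is a recruitment log by age band, one chart variable and slightly slower BPH enrolment, since some men may have to wait for an open band. If banding is impractical or enrolment is too far advanced, reporting the gain over the age-plus-diabetes model is sufficient. It works less well where the groups' ages overlap little, so the age distribution of each group should be shown beside it.

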### 6.3. Endpoints

#### 6.3.1. Overall Aim

The protocol will aim to develop and implement sensitive nanotools with two distinct objectives. It will carry this out by designing nanoparticles (NPs) capable of selectively binding and detecting biomarkers in order to build a predictive diagnostic model to effectively discriminate between patient sera affected by benign prostatic hyperplasia (BPH) and prostate cancer (PCa). This initiative will be driven by improving diagnostic precision and accuracy, enabling early and accurate differentiation between these two conditions. Secondly, within the population with PCa, in cases of initial advanced metastatic diagnosis (mHSPC = metastatic hormone-sensitive prostate cancer), the objective will be to find biomarkers capable of predicting the response to systemic treatments to improve the precision and efficiency of monitoring treatment outcomes, leveraging the aforementioned nanotechnology and leading to the development of personalized therapeutic strategies for patients.

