#### 6.3.2. Primary Endpoints

The first primary endpoint is the construction of predictive diagnostic models on serum from patients with a histological diagnosis of PCa versus patients with BPH using proteomics, metabolomics, and lipidomics of the biomolecular coronas that form between nanoparticles and serum.

A second endpoint is the construction of a predictive model for the response to treatment of patients with an initial diagnosis of mHSPC for the personalization of therapies and for the stratification of such patients considering individual characteristics such as genetics, lifestyle, and more, as foreseen by precision medicine, using metabolomics and lipidomics of the biomolecular coronas that form between nanoparticles and serum.

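### Every control has BPH by entry criterion, but coexisting BPH in the cancer cases is left open, so part of the PCa-versus-BPH discrimination may reflect absence of BPH

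*Protocol article*

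**What the plan says.** The first primary endpoint (section 6.3.2) is the "construction of predictive diagnostic models on serum from patients with a histological diagnosis of PCa versus patients with BPH". It treats PCa and BPH as two classes, although one man can have both.

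- **Controls (section 6.4.2):** Subgroup 3 consists of "male patients aged between 40 and 75 years, of any ethnicity, with an initial diagnosis of BPH". Men with suspected or diagnosed prostate cancer are excluded.
- **No other control group (section 6.4):** "A healthy control population is not included but the BPH population will be used as a control".
- **Cases (section 6.4.1):** Subgroups 1 and 2 are "Male patients aged between 40 and 75 years, of any ethnicity, with an initial histological diagnosis of PCa from prostate biopsy". Their exclusions begin with "Local or systemic therapies for PCa, other neoplasms in the active phase or undergoing treatment" and go on to concurrent oncological, hormonal and interfering therapies. BPH appears in neither list.
- **Rationale (section 6.4):** differences are to be sought "within a population with benign prostatic pathology such as BPH and not healthy subjects (those without BPH) of mismatched age".
- **Analysis (section 6.6):** PCA, then OPLS-DA for the proteomic data and PLS-DA for the metabolite data. No use of BPH status or prostate volume among cases is described. Section 6.3.3 plans, as a secondary endpoint, models relating the omics data to clinical data that are not specified.

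**The concern.** The rationale works only if cases and controls share the benign background, so that cancer is what differs between them. As written, the controls are 100% BPH and the cases are an unknown mixture of men with and without it. To the extent that cases lack BPH, class label and BPH status are confounded.

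The planned method is open to this. The metabolite assay is untargeted, the protein assay lists every protein identified, and the discriminant models are fitted to group labels. Section 6.6 counts a coordinated change across many predictors as a strength. Such a model will use any systematic difference between the groups, including one produced by benign enlargement. The issue is the disease itself, separate from any effect of BPH treatment.

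At stake is what the first primary endpoint means. A model that leans on BPH would do worst in men who have both conditions, which is where the two diagnoses most need to be told apart. A single overall accuracy figure would not show how it performs in them.

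**Working it through.** The article states no accuracy target, AUC or sample size, so there is no figure of its own to reproduce. The check asks how well a signal with **no** cancer information could appear to do under these criteria.

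**Inputs**
- Share of controls with BPH: 100% (section 6.4.2).
- Share of cases with BPH: *f*. The article does not give it, so it is an assumption and is varied.
- Sensitivity *Se* and specificity *Sp* of the signal for BPH: also assumptions. The main illustration uses 85% for both.

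**Formulas.** Call a man cancer when the BPH signal is negative.
- Apparent sensitivity for PCa = (1 − f) × Sp + f × (1 − Se)
- Apparent specificity = Se, because every control has BPH
- Balanced accuracy = (sensitivity + specificity) / 2, which simplifies to 0.5 + (1 − f) × (Se + Sp − 1) / 2

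**Results with Se = Sp = 0.85**

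| f | Apparent sensitivity | Specificity | Balanced accuracy |
|---|---|---|---|
| 0.3 | 0.7 × 0.85 + 0.3 × 0.15 = 0.64 | 0.85 | 0.745 |
| 0.5 | 0.5 × 0.85 + 0.5 × 0.15 = 0.50 | 0.85 | 0.675 |
| 0.7 | 0.3 × 0.85 + 0.7 × 0.15 = 0.36 | 0.85 | 0.605 |

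Among cases with BPH the sensitivity is 1 − Se = 0.15 whatever *f* is. That equals the false-positive rate in controls (1 − 0.85 = 0.15), so in men with BPH the signal performs at chance.

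**Varying both assumptions (balanced accuracy)**

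| Se = Sp | f = 0 | f = 0.2 | f = 0.5 | f = 0.8 | f = 1 |
|---|---|---|---|---|---|
| 1.0 | 1.00 | 0.90 | 0.75 | 0.60 | 0.50 |
| 0.9 | 0.90 | 0.82 | 0.70 | 0.58 | 0.50 |
| 0.8 | 0.80 | 0.74 | 0.65 | 0.56 | 0.50 |

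The artefact is large if few cases have BPH and the signal is strong, small if most cases have BPH, and gone at f = 1. The last column also describes an analysis confined to men with BPH: there a pure BPH signal scores 0.50, so any discrimination that remains must come from something other than BPH status. This is why reporting by BPH status answers the question.

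**The case against.** **The control group is deliberate.** The stated question is PCa versus BPH, and section 6.4 explains why men without BPH are not used. This stands: BPH controls are a legitimate choice. The gap is the open BPH status of the cases.

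**The article may simply be condensed.** Recording fields and stratified analyses often sit in a full protocol or analysis plan, and the clinical data in section 6.3.3 could include prostate volume. This stands in part: one cannot say that no analysis anywhere will use BPH status. But the asymmetry in eligibility is fixed in this article and does not match the rationale given beside it. A secondary correlation with unspecified clinical data also does not condition the first primary endpoint.

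**BPH may be common in the cases.** The age-based argument in section 6.4 can be read as treating BPH as the usual background at these ages, and then the bias would be small. That is possible, but the article gives no figure either way.

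**Stronger readings.** A reader might infer that the classifier will score well merely by detecting absence of BPH. The document does not support this. Balanced accuracy of 0.605 to 0.745 is modest, and sensitivities of 36% to 64% would be visible in any report. Values of 0.82 to 0.90 need about 20% of cases with BPH and a BPH signal at least 90% accurate, and both are assumptions. A reader might also infer that BPH status and volume are already on hand for every participant. They are not shown to be: MRI and prostatectomy belong to Subgroup 1, Subgroup 2 is staged by PET CT or by bone scan and CT, and no method of diagnosing BPH is given for Subgroup 3.

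**Conclusion.** The concern holds as a possible bias of unknown size. The criteria do not secure the comparison that section 6.4 says it wants, and part of the discrimination found may be due to absence of BPH in some cases. Under the illustrative 85% signal, balanced accuracy without any cancer information would run from 0.745 to 0.605 as the share of cases with BPH goes from 30% to 70%, with 15% sensitivity in cases that have BPH. Both the strength of the signal and the share of cases with BPH are assumptions; nothing in the article shows that a corona signal of that strength for BPH exists.

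This does not show that the control group is wrong or that the classifier will fail. Nor does it require the primary claim to rest only on cases with BPH: that subset is of unknown size, and tying the claim to it would be a debatable trade-off. What follows is that overall accuracy, reported alone, cannot be read as evidence of cancer detection in men with BPH. The plan should address this.

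**What to change.** 1. **Record coexisting BPH and prostate volume in Subgroup 1**, from the staging MRI and the biopsy or prostatectomy histology that these patients already have. In Subgroups 2 and 3, record them where existing records provide them, and report how many are missing.
2. **Report the first primary endpoint's sensitivity separately for cases with and without BPH**, mainly in Subgroup 1, next to the common specificity in Subgroup 3.
3. **Add volume-adjusted discrimination as a sensitivity analysis**, among participants with a recorded volume.
4. **State in the plan and in the report** that overall accuracy alone does not show cancer detection in men with BPH.

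Eligibility, sampling and treatment stay as they are. The cost is two data fields and one stratified report in Subgroup 1, and somewhat more effort and incomplete data in Subgroups 2 and 3. Intervals within strata will be wider, and the headline accuracy may turn out lower. The fields are best defined before enrolment, since BPH status is harder to establish reliably afterwards.

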## 3. Potential Diagnostic Role in Oncology

Early cancer detection methods are needed, as currently available tests can detect only a small fraction of potential biomarkers. Recently, significant advancements have been made in proteomic analysis, with nanotechnology-based platforms emerging as promising tools [9].

Nowadays, it is well known that the protein pattern in the blood of cancer patients differs from that of healthy donors, and the molecular composition of the protein corona around NPs could change between patients with and without cancer, although the exact causes are not clearly defined. Hundreds of plasma proteins are differentially expressed, whether increased or decreased, as a cause or consequence of cancer. Consequently, the identity of NPs might be affected by protein alteration in the blood of cancer patients [10]. Researchers demonstrated that the protein corona composition could also be influenced by tumor size and the presence of distant metastases [11]. Routinary blood tests are not able to characterize each profile. The NPs’ corona characterization could detect minor changes in protein concentration either in early cancer stages or even after primary treatment (chemotherapy, surgery, etc.) [9]. A novel platform has been developed for NPs’ protein corona detection, combining the basic ideas of disease-specific protein coronas with sensor array technology. This platform consists of three cross-reactive liposomes with systematic changes in surface charge, incubated with plasma collected from diagnosed cancer patients. The resulting coronas are subsequently thoroughly characterized by several methods [11].

Different examples regarding the potential role of protein coronas–NPs as biomarkers for neoplasms are available in the literature.

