### 6.6. Statistical Analysis

In the analytical field, we often work with complex problems in which the variables are numerous and sometimes uncontrollable; furthermore, information may be difficult to extract due to the presence of experimental noise, random or systematic correlations between variables, and useless or redundant variables. It is therefore essential, for a correct interpretation of the analytical data, to eliminate redundant and superfluous information to evaluate which are the most significant variables and consider any correlations between them.

For proteomics analysis, statistics and multivariate data processing will be carried out. A three-dimensional data matrix consisting of sample information, identified peptides, and the normalized ion intensity will be generated. The resultant three-dimensional matrix will be imported to SIMCA-P 14.1 software (Umetrics AB, Umeå, Sweden) for multivariate statistical analysis, including principal component analysis and orthogonal partial least squares discriminant analysis (OPLS-DA). The functional analysis of differentially expressed proteins will be performed using Gene Ontology (GO). The strength of this approach lies not only in pinpointing individual predictors (i.e., single biomarkers) but also in the pattern recognition enabled by a protein corona sensor array. The differentiation between the groups of samples may arise due to a “global change” involving several predictors that are systematically altered simultaneously, resulting in distinctive global protein patterns unique to the pathological conditions. By concentrating on unique patterns derived from a large number of subjects through a set of informative predictors, we will achieve more accurate predictions of PCa and different stratified mHSPCa patients than current methods allow.

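### The diagnostic claim covers PCa in general and early differentiation, but localised cases are limited to intermediate- or high-risk men indicated for prostatectomy

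*Protocol article*

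**What the plan says.** **Claim.** Section 6.3.1 of the protocol article sets the first objective as a diagnostic model to separate BPH from PCa, "enabling early and accurate differentiation between these two conditions". The first primary endpoint (6.3.2) is model construction on "serum from patients with a histological diagnosis of PCa versus patients with BPH". Neither sentence limits the risk class. Section 6.6 expects that "we will achieve more accurate predictions of PCa and different stratified mHSPCa patients than current methods allow", and section 7 speaks of telling benign from malignant prostatic disease, again without a limit.

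**Enrolment.** For localised disease, the criteria in 6.4.1 require "intermediate or high-risk class according to d’Amico, indication as primary treatment for radical prostatectomy (Subgroup 1"). This group is non-metastatic on imaging. The other PCa group is mHSPC, and its members enter with an indication for "systemic therapy with androgen deprivation and ARPI or taxanes (Subgroup 2"). Controls are men with BPH, excluding any with "suspicion or diagnosis of prostatic neoplasia" (6.4.2).

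**Background.** Section 3 says of cancer in general that "protein corona composition could also be influenced by tumor size and the presence of distant metastases".

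**The concern.** A diagnostic model learns from the cases it is given. Here the low-risk end of newly diagnosed PCa is absent by rule, as is localised disease not treated by surgery. If the corona signal weakens as the tumour becomes smaller or less aggressive, the missing men are the ones hardest to separate from BPH, and sensitivity measured in the enrolled men would be too high for PCa as a whole.

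At stake is the conclusion on the first primary endpoint. A good result would be read, in the plan's own words for the target, as applying to PCa at first diagnosis, although part of that population was never sampled. No analysis plan can repair this, because the data on those men will not exist.

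**Working it through.** **Step 1. Set claim against enrolment.**

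| Type of PCa | Inside the stated target (6.3.1, 6.3.2)? | Route into the study (6.4.1)? |
|---|---|---|
| Low-risk localised | Yes | None |
| Intermediate/high-risk localised, not for prostatectomy | Yes | None |
| Intermediate/high-risk localised, for prostatectomy | Yes | Subgroup 1 |
| Metastatic (mHSPC), systemic therapy | Not stated whether it enters the diagnostic model | Subgroup 2 |

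No other section narrows the diagnostic claim.

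**Step 2. What the article says about direction.**
- Sections 3 and 5.1 contain evidence that the signal may grow with disease extent. In 20 pancreatic cancer samples, T1-T2 cases were distinguished from T3 and especially from metastatic cases. In mice, the mean particle-size increase was 75 nm in controls, 43 nm with the slow prostate line and 24 nm with the fast one. The slow-line range (20 to 110 nm) overlapped the control range (40 to 120 nm).
- Section 5.1 also contains evidence the other way. In 60 men (20 healthy, 20 BPH, 20 PCa) corona size did not differ significantly between groups.
- Nothing links D'Amico class to corona signal in men.

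An upward bias is therefore plausible, not demonstrated.

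**Step 3. Size.** The article gives no sensitivity, specificity or risk mix, so there is no figure to reproduce. The following is an illustration in which every input is an assumption.

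Let *w* be the share of newly diagnosed PCa that the criteria leave out, Se_IH the sensitivity in enrolled intermediate/high-risk men (assumed 0.90), and Se_ex the sensitivity in the men left out.

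Se_target = (1 − w) × Se_IH + w × Se_ex

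Overstatement = Se_IH − Se_target = w × (Se_IH − Se_ex)

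Example: w = 0.25 and Se_ex = 0.70 give Se_target = 0.75 × 0.90 + 0.25 × 0.70 = 0.85, an overstatement of 5 points.

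| w | Se_ex 0.90 | 0.80 | 0.70 | 0.50 |
|---|---|---|---|---|
| 0.10 | 0 | 1 | 2 | 4 |
| 0.25 | 0 | 2.5 | 5 | 10 |
| 0.40 | 0 | 4 | 8 | 16 |

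(percentage points, Subgroup 1 alone as cases)

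**Step 4. If Subgroup 2 were pooled.** Section 6.2 describes a design "with patients allocated in a 1:1:1 ratio of one of the three arms". Pooling Subgroups 1 and 2 equally, with an assumed sensitivity of 0.95 in metastatic men, gives (0.90 + 0.95)/2 = 0.925. That adds 2.5 points to each cell, for a range of 2.5 to 18.5. This step keeps the Step 3 target, which gives metastatic men no separate weight; including them in the target would offset part of the 2.5 points.

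**The case against.** **The strongest case against.** Enrolling a defined disease class in a single-centre model-building study is a legitimate choice, and the criteria are openly stated. The endpoint is construction of a model, with no sensitivity target to be wrong about. *Early* in 6.3.1 can mean early in the diagnostic pathway rather than low-risk disease. Subgroup 1 is untreated, non-metastatic and at first histological diagnosis, so it bears directly on telling localised PCa from BPH. Section 6.3.3 also plans to correlate the omics data with clinical data in each population.

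**What of it stands.** The design choice is defensible, and this point does not ask to change it. Four stronger readings that a reader might reach are not supported:

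- *That all PCa enrolment is limited to surgical candidates.* Subgroup 2 enrols metastatic men on systemic therapy.
- *That the model cannot serve the aim at all.* It can inform intermediate/high-risk localised PCa versus BPH.
- *That sensitivity will certainly be overstated, by a known amount.* Assuming 20 to 40% low-risk disease, with sensitivity of 85% in enrolled men and 50 to 65% in low-risk men, gives 4 points (0.85 − 0.81) to 14 points (0.85 − 0.71). That range leaves out zero only because it starts from an assumed fall of 20 to 35 points.
- *That the conclusions promise early differentiation.* Section 7 does not; the word is attached to the diagnostic aim in 6.3.1.

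**What does not stand.** Open eligibility criteria do not cure an aim and endpoint worded for a wider population. Correlation with clinical data in the enrolled groups says nothing about men outside them.

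**Conclusion.** The point holds as a mismatch between the claimed and the enrolled population. Aim, endpoint and criteria are all stated in the article, so the mismatch does not depend on anything left to a fuller document. Results can be claimed for non-metastatic intermediate- or high-risk PCa in men indicated for prostatectomy, against BPH without suspected neoplasia. They cannot be extended to low-risk or unselected newly diagnosed PCa.

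Overstated sensitivity for that wider population is likely but not certain. It rests on the assumption that the excluded men give a weaker signal, for which the article's support is general, pancreatic or from mice, with one human prostate study reporting no difference in corona size. The amount cannot be estimated from the article. The 0 to 16 points are illustrative, and the value is zero if the excluded men are detected as well as those enrolled.

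**What to change.** - In 6.3.1 and 6.3.2, state the diagnostic target as non-metastatic intermediate- or high-risk PCa versus BPH. This also settles that Subgroup 2 is outside the diagnostic comparison.
- In 6.3.1, remove *early*, or define it as localised disease at first diagnosis.
- Limit the accuracy claim in 6.6 and the benign-versus-malignant claim in section 7 in the same way.
- Report sensitivity with confidence intervals separately for intermediate- and high-risk men, using the D'Amico class that eligibility already requires, so that any fall towards lower risk is visible.

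**Cost.** Wording in four sections and one stratified table, with no extra patients, samples or procedures. The claim becomes narrower. The stratum estimates will be imprecise; the article states no sample size, so how imprecise cannot be said here.
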